## Exploratory outcomes

To identify any association between the use of different endovascular techniques or open surgical configuration and subsequent outcomes (amputation free survival).

# TRIAL DESIGN and setting

The EVOCC trial is a two-arm prospective, superiority, multicentre (national), randomised controlled trial (RCT) comparing two modes of treatment which are already routine NHS care, in over30 UK sites (NHS hospitals which already provide care for PAD to patients). Open surgery will be compared to the newer treatment (intervention) using established methodology and pre-specified plans by the CTU team and statisticians. This will address the existing uncertainty whether surgery is superior (clinical and cost-effectiveness) to endovascular treatment. Blinding is impossible in this setting given the completely different nature of the two trial treatments.

Thirty NHS hospital vascular networks which routinely provide care to patients with PAD have confirmed they will take part, across a wide geographical spread (urban and rural); the sites treat a diverse (ethnically and socioeconomically) PAD population, with high prevalence of amputations and diabetes.

The target population is individuals ≥18 years with severe occlusive aorto-iliac disease (TASC II C or D class) presenting with ischaemic lower limb rest pain and/or tissue loss and/or lifestyle limiting claudication to NHS vascular hospital networks. Patients will be screened and recruited across all secondary care settings in those hospitals (clinic, ward, on-call, remote referrals). Randomisation will take place as soon as the patient provides written informed consent. Patients undergoing these treatments in the NHS are usually discussed at multidisciplinary (MDT) team meetings. The patients will be approached for consent once the MDT feel are in equipoise regarding the treatments.

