**TRIAL FLOW CHART**

Setting NHS Hospitals providing specialist care to patients with PAD

Patients with severe occlusive aorto-iliac PAD presenting with symptomatic peripheral arterial disease [rest pain and/or tissue loss (gangrene) and/or life style limiting claudication], already being considered for revascularisation

Screening & enrolment

**Inclusion criteria:** patient deemed eligible for both open & endovascular procedure

**Exclusion criteria:** Age ≤18 years, Asymptomatic PAD

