# BACKGROUND

The clinical and cost-effectiveness of open surgery vs. minimally invasive endovascular treatment for severe occlusive aortic and iliac artery disease is unknown. This area has been identified as a research priority in a recent James Lind Alliance (JLA) process across several vascular disease areas, such as peripheral arterial disease (PAD), diabetic foot care, and amputations (1).

Lower limb Peripheral Arterial Disease (PAD) affects 20% of people over 55 years of age (2) and is the main cause of amputations in the NHS (2). Often, patients with PAD develop leg pain when walking (called claudication). Some patients might also develop leg pain at rest or lower limb necrosis, a condition called Chronic Limb Threatening Ischaemia (CLTI) (3). This is limb and life threatening and requires urgent revascularisation to save the patient’s limb/life (3). The aorta and iliac arteries are common sites affected in people with lifestyle limiting claudication or CLTI (4). These patients can have revascularisation either with open surgery or more recently developed minimally invasive techniques in the form of endovascular treatment (3). Both open surgery and endovascular treatment, however, are associated with significant complications. Open surgery is associated with a 3% early mortality and many perioperative complications (5). Endovascular treatment is less invasive, with a 1% early mortality rate (5, 6). Endovascular devices, however, are costly and 43% of patients need re-intervention within 3 years (5).

Patients in our study development focus groups expressed a preference for endovascular treatment. They were, however, concerned about the many re-interventions and high number of late deaths or amputations potentially associated with endovascular treatment. Some patients even voiced concerns about the high cost of the endovascular devices and many re-interventions. There is no randomised evidence comparing the clinical and cost-effectiveness of these techniques in this context, potentially leading to more deaths, amputations, and increased NHS costs. Clinicians therefore do not know which treatment to offer this cohort. The need to improve outcomes and reduce amputations in CLTI/claudication has been highlighted by the JLA and Vascular Society of Great Britain and Ireland (VSGBI) in 2021 as a key research priority (1).

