# Eligibility criteria

## Main trial criteria

### Inclusion criteria

- Age ≥18 years (no upper age limit)
- Presence of symptomatic PAD (tissue loss and/or rest pain and/or lifestyle limiting claudication)
- Severe aorto-iliac occlusive PAD defined as “Inter-Society Consensus for the Management of Peripheral Arterial Disease” (TASC II) class C or class D diagnosed on prior cross-sectional imaging
- Patient discussed in any local vascular Multi-Disciplinary Team (MDT) meeting/discussion and deemed suitable for open surgery or endovascular treatment.
- Patient willing and able to give consent and commit to study follow-up.
- An ability to understand written English or availability of a translator to explain the trial documentation

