## Randomisation

After the consent form has been signed, the participant will be randomised to receive one of the two arms; open surgery or endovascular treatment. Participants will be randomised via the 24 hour, web-based service, Sealed Envelope.

Random allocations will have a 1:1 ratio, will be minimised by the following variables: age above 65 years, sex, and presence of tissue loss (yes/no) and stratified by site. Randomisation forms should be completed alongside online randomisation. After a participant is randomised, the user is presented with the allocated treatment group and the unique Participant ID Number. A notification email will be sent to the person conducting the randomisation, copying in Leicester Clinical Trials Unit via the EVOCC trial mailbox. The Participant ID number must be entered onto the participant signed ICF and all CRFs from this point forward and will link the participant details to the trial data. Any errors in the randomisation process should be reported to Leicester Clinical Trials Unit as soon as reasonably possible after being identified.

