| **Expected SERIOUS Adverse Events** | The following events are considered as expected SAEs. For the purposes of this trial such events do **NOT** require reporting to the EVOCC central team or Sponsor. These events should continue to be recorded in the medical records according to local practice and on the routine follow-up CRFs.   \| Bowel obstruction \| \| --- \| \| Acute kidney injury \| \| Arterial dissection \| \| Arterial pseudoaneurysm formation \| \| Atrial fibrillation (new) \| \| Bowel ischaemia \| \| Chest infection \| \| Diabetes (new diagnosis) \| \| Diabetic foot ulcer (new) \| \| Diabetic ketoacidosis \| \| Endovascular re-intervention (will have to be reported separately using the relevant form) \| \| Failure of endovascular closure device \| \| Fall \| \| Fasciotomy \| \| Haematoma (at site of surgery or percutaneous puncture) \| \| Heart failure (non-fatal) \| \| Hernia \| \| Hypertension (new diagnosis) \| \| Ileus \| \| Intermittent claudication (new diagnosis) \| \| Laparotomy \| \| Lower limb compartment syndrome \| \| Lower limb oedema \| \| Minor amputation (below the ankle joint) \| \| Myocardial infarction (non-fatal) \| \| Need for open surgical access to an artery during the index endovascular procedure \| \| Peripheral embolisation \| \| Peripheral embolisation, not requiring surgery or re-intervention \| \| Prescription of antibiotics for lower limb tissue loss (ulcer/gangrene) \| \| Re-admission to hospital within 30 days of randomisation \| \| Requirement for catheterisation (urinary catheter) \| \| Stent or graft occlusion \| \| Stent or graft thrombosis \| \| Stoma formation \| \| Stroke \| \| Surgical re-intervention (will have to be reported separately using the relevant form) \| \| Transient ischaemic attack \| \| Transient renal replacement therapy \| \| Urinary retention \| \| Urine infection \| \| Use of additional stent or additional endovascular device \| \| Venous thrombosis (deep and/or superficial) \| \| Viral infection \| \| Wound infection \| |

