## Primary outcome analysis

The primary analysis of the primary outcome (amputation free survival) will compare the time to first event between randomised groups. The primary outcome will be defined as time to first event calculated by measuring in days the time from randomisation until first event or last known event-free observation during the follow-up period. Participants not experiencing a primary outcome event will have their time to event censored at last follow-up date. Participants withdrawing consent or that are lost to follow-up prior to reaching primary outcome will have their time to event at last contact date. The primary analysis will be undertaken on an intention-to-treat basis with all participants included post randomisation analysed in the group to which they were allocated. The primary outcome will be compared between randomised arms using restricted mean survival time carried out using a validated programme such as the Stata module ‘STRMST2’ or equivalent. A point estimate, 95% confidence interval and 2 sided p-value will be presented. Statistical significance will occur if the p-value is <0.05. The primary analysis will be adjusted for the minimisation factors used at randomisation. The individual components of the primary outcome will be reported separately as secondary outcomes

Secondary analyses of the primary outcome will explore a per-protocol population excluding major protocol deviators.

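### The primary analysis adjusts for limb severity only through tissue loss yes/no, which pools rest pain with claudication and forgoes a small, cheap gain in precision

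*Protocol*

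**What the plan says.** Section 5 (Trial design and setting) describes the target population as patients "presenting with ischaemic lower limb rest pain and/or tissue loss and/or lifestyle limiting claudication", and section 6.1.1 admits the same three presentations.

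Section 1 (Background) treats claudication as the common presentation and then says: "Some patients might also develop leg pain at rest or lower limb necrosis, a condition called Chronic Limb Threatening Ischaemia (CLTI"). It goes on to describe CLTI as a threat to limb and life.

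Section 8.3 (Randomisation) minimises on "age above 65 years, sex, and presence of tissue loss (yes/no) and stratified by site". Section 11.1 defends these factors as the principal predictors of outcome in earlier studies and similar trials.

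Section 11.5 (Primary outcome analysis) states: "The primary analysis will be adjusted for the minimisation factors used at randomisation". No other measure of limb severity enters that model. TASC class appears only among the exploratory subgroups in section 11.6.1. Table 2 has no separate baseline item for presenting symptom.

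**The concern.** The Background draws its clinical line between claudication on one side and rest pain or necrosis on the other. The covariate draws the line elsewhere:

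| Presentation | Background | Level of the covariate |
|---|---|---|
| Claudication only | not CLTI | tissue loss: no |
| Rest pain, no tissue loss | CLTI | tissue loss: no |
| Tissue loss | CLTI | tissue loss: yes |

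The primary outcome is death or major amputation, which are the hazards the Background attaches to CLTI. If rest pain carries a higher risk than claudication, the 'no' level mixes two risk groups. The difference between them then stays in the residual variance, and the confidence interval for the RMST difference is wider than it needs to be. Presentation has to be established for every participant to confirm eligibility, so the information should exist before randomisation.

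**Working it through.** **1. The plan's own figures (section 11.1).**
- Endovascular 3-year event-free proportion: (1 − 0.2063)³ = 0.500, as stated.
- Hazard ratio: ln 0.633 / ln 0.5 = 0.660, as stated.
- Events from 298 per arm, with exponential survival and follow-up uniform on 24 to 48 months: 147.7 + 108.6 = 256.3 (stated 256).
- 596 / 0.95 = 627.4, rounded up to 628, as stated.
- RMST to 36 months, (1 − e^(−36λ))/λ: λ = 0.01925 per month gives 25.97 months and λ = 0.01270 gives 28.89. The difference is 2.92 months (stated 3).

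The figures reproduce, and section 11.1 takes no credit for covariate adjustment.

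**2. What the third level adds.** Let each presentation g have share p and constant hazard λ. For min(T, 36 months) it has mean m = (1 − e^(−36λ))/λ and variance v = 2[1/λ² − e^(−36λ)(36/λ + 1/λ²)] − m². Adjusting for three levels leaves residual variance Σpv in an arm. Adjusting for tissue loss yes/no leaves that plus the spread between claudication (1) and rest pain (2):

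extra = [p₁p₂/(p₁ + p₂)] × (m₁ − m₂)²

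The standard error of the RMST difference is √[(sum of the two arms' residual variances)/298].

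**3. Assumed inputs.** The protocol gives no symptom shares and no event rates by presentation. Five mixes of claudication/rest pain/tissue loss were tried: 50/25/25, 30/35/35, 40/20/40, 60/20/20 and 34/33/33. In each arm the claudication hazard is set so that the overall 3-year event-free proportion is 50% (endovascular) or 63.3% (open). The 36-month horizon is also an assumption, because the protocol names none.

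**4. One case in full: mix 50/25/25, hazards 1, 2, 3.**
- Endovascular: claudication hazard 0.01194 per month; means 29.26, 24.15 and 20.23. Extra = (0.125/0.75) × (29.26 − 24.15)² = 4.36. Residual variance 147.77 with two levels, 143.42 with three.
- Open: claudication hazard 0.00766; means 31.47, 27.68 and 24.49. Extra = (0.125/0.75) × (31.47 − 27.68)² = 2.39. Residual variance 123.00 with two levels, 120.61 with three.
- Standard error: √(270.77/298) = 0.953 with two levels, √(264.02/298) = 0.941 with three.
- Variance ratio: 264.02/270.77 = 0.975, a 2.5% reduction.
- The RMST difference is 3.05 months. Power is Φ(3.05/0.953 − 1.96) = 89.2% with two levels and Φ(3.05/0.941 − 1.96) = 90.0% with three.

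**5. Range over the five mixes.**

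| Hazard vs claudication: rest pain, tissue loss | Variance reduction | Power gain (points) |
|---|---|---|
| 1, 2 | 0 | 0 |
| 1.5, 2.5 | 0.6–0.8% | 0.2–0.3 |
| 2, 3 | 1.7–2.5% | 0.5–0.7 |
| 3, 4 | 4.1–6.7% | 1.1–1.7 |
| 3, 6 | 3.3–6.3% | 0.7–1.2 |

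In sample-size terms, 1.7–2.5% of 596 is about 10 to 15 patients, and 6.7% is about 40. At extreme hazards (4 and 6) the variance reduction can reach 9% or more, but the power gain still stays under 2 points. The calculation leaves out age and sex, which are in the planned model, so the true gain is probably slightly smaller. It also ignores censoring before 36 months. That matters little: with follow-up uniform on 24 to 48 months, the unadjusted standard error moves only from 0.969 to 0.972.

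**The case against.** Adjusting for the factors used in the allocation is standard practice, and sections 8.3 and 11.5 agree with each other. Section 11.1 gives a reason for the choice, and the studies behind it cannot be examined here. The Background gives no event rates by presentation, so the documents do not prove that rest pain does worse than claudication. If it does not, the gain is zero. Further covariates could also be added in the statistical analysis plan. All of this stands, and it limits the point to a missed efficiency. What remains is that section 11.5 itself fixes the covariate set, and that the set cuts across the protocol's own clinical grouping.

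A reader might infer more than the documents support:
- **Bias, or a flaw through chance imbalance.** Allocation is randomised 1:1, and the confidence interval already allows for chance imbalance in a factor that is not adjusted for.
- **An underpowered trial.** Under exponential survival, unadjusted RMST power is about 85% at an assumed 36-month horizon but 90.7% near 47.5 months. The protocol states no horizon, so the lower figure is not a failure of the plan.
- **Miscoding of ulcers.** The flow chart writes "rest pain and/or tissue loss (gangrene) and/or life style limiting claudication" and the list of expected serious events writes "Prescription of antibiotics for lower limb tissue loss (ulcer/gangrene"). Neither defines the minimisation variable. Sites complete a randomisation form that is not shown, and nothing indicates that they code from the flow chart.

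**Conclusion.** The point holds as a modest missed gain in precision. The only limb-severity covariate in the primary model places rest pain, which is CLTI by the protocol's own description, with claudication. For a rest-pain hazard of 1 to 3 times that of claudication, a three-level covariate lowers the variance of the RMST difference by 0 to about 6% (6.7% at most in the cases tried) and adds 0 to about 2 points of power. The direction follows if the Background is right that CLTI has the worse prognosis. The size depends wholly on the assumed mix, hazards and 36-month horizon. Validity, target of estimation, minimisation and sample size are unaffected. The change is worth making because it costs little.

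**What to change.** In section 11.5, keep age, sex and the handling of site as planned. Prespecify, before any outcome data are seen, that severity enters the primary model as presenting symptom in three levels: claudication only; rest pain without tissue loss; tissue loss. These levels nest the minimisation factor, so the analysis still respects the allocation and randomisation does not change.

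Use the status documented at the eligibility or multidisciplinary assessment before randomisation. The baseline visit in section 8.4.1 follows allocation in an open-label trial, so a symptom first classified there could be influenced by knowledge of the arm.

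The cost is one model term and one baseline field, since Table 2 does not list presenting symptom separately. For participants already enrolled, the field has to be completed from records made before randomisation. The change is therefore cheap, though not entirely free.

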## Internal pilot and progression criteria

Given the complexities relating to the recruitment of individuals with symptomatic PAD, an internal pilot phase has been planned based on NIHR guidance, national surveys, audits and HES data. The progression criteria have been calculated based on the requirement to recruit 628 eligible patients from 30 sites during a 30 month recruitment period (including the internal pilot involving 10 sites). Recruitment rates and progression criteria have been based on completed NIHR HTA trials recruiting patients with symptomatic PAD. Assuming a very conservative ~6% consent rate, the aim is to recruit at least 1 participant per site per month during the pilot phase and subsequently in the main trial phase.

**Proposed pilot length**: The 6 month internal pilot will commence following a 6 month trial set up and regulatory approval period and 3 month period for pilot site set up (overall 9 months for set up). At least 10 sites will open to recruitment for the 6 month duration of the internal pilot. This will also allow the qualitative Bristol QuinteT team to conduct interviews and qualitative assessments at each of these sites. Upon successful recruitment and site set ups, the trial will progress to recruit from over 30 sites for an additional 24 months. The Trial Steering Committee (including PPI partners and CTU representation) will meet at the end of the pilot recruitment period (project month 16) to assess progression criteria, summarised in Table 1.

**Progression criteria:** Green, proceed to main phase (100% of all targets achieved); Amber, reflect, remodel, and adjust project plan in consultation with funder [75%-99% (minimum) of all targets achieved]; Red, trial stopped (<75% of any target achieved).

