**Table 1. Internal Pilot progression criteria**

| **Progression criteria** | **Red** | **Amber** | **Green** |
| --- | --- | --- | --- |
| **% Threshold** | <74% | 75-99% | **100%** - all below criteria must be met to proceed directly to main recruitment phase. |
| **Recruitment rate/site/month** | ≤ 0.74 participants per month per site | 0.75 to 0.99 participant per month per site | ≥ 1.0 participant per month per site |
| **Number of sites opened by the end of the pilot phase** | ≤ 6 | 7 to 9 | ≥10 |
| **Total number of participants recruited** | ≤ 44 across all pilot sites over 6 months | 45 to 59 across all pilot sites over 6 months | ≥ 60 across all pilot sites over 6 months |

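### Opening 7 of 10 pilot sites is Red (stop) under the text of Protocol section 5.1 but Amber in Table 1, and the Red cut-off is given as both 75% and 74%

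*Protocol*

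**What the plan says.** The progression paragraph in Protocol section 5.1 defines three outcomes as percentages of target:

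- Green: "Green, proceed to main phase (100% of all targets achieved".
- Amber: "75%-99% (minimum) of all targets achieved".
- Red: "Red, trial stopped (<75% of any target achieved".

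Table 1, which the same section presents as the summary of these criteria, turns them into cut-offs on three rows:

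- Recruitment rate: Green is "≥ 1.0 participant per month per site", Amber is 0.75 to 0.99, and Red is 0.74 or less.
- "Number of sites opened by the end of the pilot phase": Green is 10 or more, Amber is 7 to 9, and Red is 6 or fewer.
- Total recruited: Green is "≥ 60 across all pilot sites over 6 months", Amber is "45 to 59 across all pilot sites over 6 months", and Red is "≤ 44 across all pilot sites over 6 months".

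The percentage row at the top of the table gives Red as below 74% and Amber as 75 to 99%.

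**The concern.** A progression rule fixed in advance should return one answer for any set of pilot results. Here the same result, 7 sites opened, is a stop under the paragraph and a reflect-and-adjust under the table. The committee applying the rule, and anyone later reading the pilot report, cannot tell from the protocol which one governs. The consequences differ sharply, since Red stops the trial and Amber leads to a revised plan agreed with the funder. The 74% header is a second, smaller disagreement in the same place.

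**Working it through.** **Inputs.** The targets are a rate of 1.0 per site per month, 10 sites and 60 participants (Table 1). The stop threshold is 75% of any target (section 5.1 text). The basis of the targets is 10 sites recruiting 1 per month for 6 months (section 11.2).

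**Reproducing the plan's own figure.** 10 sites × 1.0 per month × 6 months = 60, which matches the Green total.

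**Applying the text's 75% to each row.**

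- Rate: 0.75 × 1.0 = 0.75. Table 1 starts Amber at 0.75, so it agrees.
- Total: 0.75 × 60 = 45. Table 1 starts Amber at 45, and 44/60 = 73.3% is Red. It agrees.
- Sites: 0.75 × 10 = 7.5. In whole sites, Red should be 7 or fewer and Amber 8 to 9. Table 1 has Red at 6 or fewer and Amber at 7 to 9. It disagrees.

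| Sites opened | Share of 10 | Section 5.1 text | Table 1 |
| --- | --- | --- | --- |
| 6 | 60% | Red | Red |
| 7 | 70% | Red | Amber |
| 8 | 80% | Amber | Amber |
| 9 | 90% | Amber | Amber |
| 10 | 100% | Green | Green |

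Only the value 7 changes band.

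**When the mismatch would decide the outcome.** Seven sites open for all 6 months give at most 7 × 6 = 42 site-months. At the target rate of 1.0 they recruit 42, which is Red on the total row whichever site rule is used. To avoid Red on the total they need 45/42 = 1.07 per site per month. So the site row alone determines stop or continue only if exactly 7 sites open and they recruit at least 45 between them.

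**The Red header.** No site count out of 10 lies between 74% and 75%. No total out of 60 does either (44 is 73.3%, 45 is 75%). Only the rate can. A rate of exactly 0.74 is Red by its own row but is not below 74%. A rate just above 0.74 and under 0.75 is Red by the text and in no band of the table.

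**The case against.** The best defence is that this is rounding. Three quarters of 10 sites is 7.5, and someone had to choose a whole number. The mismatch touches one value, the other two rows are exact, and the 74% header has almost no practical reach. The planned decision is also past. With a grant start of 01/01/2023 (Trial Summary), project month 16 falls at about April 2024, and version 3.0 is dated 30 July 2025 (Appendix 1). Nothing shows that the pilot ended with 7 sites. All of this stands and keeps the point minor. It does not remove the disagreement, because 7 is below 7.5 and the text makes no allowance for rounding.

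A reader might go further and infer that the rows contradict each other, since a pilot could be Green on sites and on rate yet Red on total. The documents do not support that. The three rows are separate criteria, and the text lets a shortfall on one target decide, so that case has a single answer, Red. It also cannot arise on the stated plan, in which at least 10 sites are open for the whole 6 months: at 1.0 per site per month they reach 60. It needs staggered opening and a rate calculated per open site-month, and the protocol does not specify that divisor. If the rate is divided by 10 × 6, the case is impossible.

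A reader might also infer that the progression decision was taken wrongly. The protocol reports no pilot result, so nothing can be said about that.

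**Conclusion.** The conflict is real but narrow. Under the text, 7 sites stops the trial; under Table 1 it does not. Every other site count, and every total, falls in the same band under both. The 74% header is a slip that can matter only for a rate between 0.74 and 0.75. This rests on reading the site target as 10, which is Table 1's Green cut-off and the basis given in section 11.2, and on applying the text's percentage to each target as written. The primary analysis, the sample size and the participants are not affected. It is a minor correction to a stated decision rule.

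**What to change.** Keep one rule, in one of two ways:

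- set Table 1's site row to Red at 7 or fewer and Amber at 8 to 9, so that it follows the 75% in the text; or
- state in the text that the cut-offs in Table 1 govern where they differ from the percentages.

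In either case change the Red header in Table 1 from below 74% to below 75%. If the progression decision has already been taken, say in the pilot report which site threshold was applied and give the result on each row.

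Leave the total target at 60. Rescaling it to the number of open site-months might look like a tidy alternative, but it would only restate a rate per open site-month, and it would remove the one absolute target that catches slow site opening.

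The cost is the wording of one paragraph and one table, with no change to data collection or analysis.
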